## Discussion

### Overview

Effective communication is fundamental to patient-centered care, yet achieving it remains challenging in practice. Our protocol describes two novel RCTs addressing a simple but prevalent problem: patients often do not fully understand the written medical information that accompanies their care, which can hinder meaningful dialogue with their doctors. By leveraging AI to translate “doctor language” into “patient language,” we aim to enhance understanding and thereby improve various facets of communication.

The Discussion section examines the rationale for and potential implications of our intervention in light of existing literature, as well as the strengths and limitations of this study design.

### Interpretation of the Intervention’s Potential Impact

If our hypothesis is correct, patients who receive an easy-to-read summary of their medical documents will feel more informed and engaged during consultations. Previous research strongly suggests that when patients comprehend their health information, several positive downstream effects occur. They are more likely to ask questions and participate in decision-making, which is a core aspect of patient-centered communication [2]. They may also experience reduced anxiety because uncertainty is diminished, as an informed patient is less likely to fear the unknown.

A classic review by Stewart [1] found that effective physician–patient communication positively influences outcomes ranging from emotional health to symptom resolution. Our intervention specifically targets the information exchange component of communication [2], aiming to make it more bidirectional and understandable. According to the model of Ong et al [2], better exchange of information, alongside a good interpersonal relationship, should improve patient satisfaction, recall, and adherence. We are measuring satisfaction with communication through FAPI and autonomy support through HCCQ, both of which we expect to improve. Autonomy support, in particular, could be enhanced because patients with preobtained knowledge might feel more control over the conversation and subsequent decisions [11]. This aligns with self-determination theory, which emphasizes that supporting a patient’s autonomy, for instance by providing choices or acknowledging their perspective, leads to better motivation and adherence to treatment plans. In our context, giving the patient information in advance is a way of respecting their role in the decision process, effectively saying, “we want you to understand and be an active partner.” We anticipate this will be reflected in higher HCCQ scores in the intervention group, indicating that patients feel their doctors were more autonomy-supportive. Notably, even without specific training for doctors, an intervention that educates patients can indirectly change the communication dynamic, as doctors might notice the patient is well-prepared and accordingly have a more nuanced discussion rather than spending most of the time explaining basics.

For physicians, one might worry that more informed patients could be more challenging, reflecting the stereotype of the patient arriving with a stack of internet printouts. However, research often contradicts this worry: physicians generally appreciate when patients have some baseline knowledge, provided it is accurate, because it can save time and lead to more focused questions [7]. Difficult physician–patient interactions often stem from misalignment of expectations or repeated explanation of basic issues [13]. We posit that our summaries will alleviate those factors, which is why we measure DDPRQ-10 to determine whether doctors find these conversations less frustrating or difficult. A reduction in “difficult” encounters is beneficial not only for patient care but also for physician well-being. Studies show that perceived difficult encounters correlate with physician burnout and suboptimal care [12]. If a simple intervention can reduce that strain, it represents a win–win. Of course, we must be cautious: it is possible that some doctors might feel the AI summary could undermine their role as information-giver or they might worry about inaccuracies. We have attempted to mitigate these concerns by involving physicians in validating the summaries and making clear that the tool is an aid, not a replacement for their explanations.

### Comparison With Related Work

Our approach draws upon previous work in health literacy and patient education interventions. There have been efforts to rewrite medical documents in simpler language manually. For instance, Smolle et al [7] simplified discharge instructions, and found improved patient comprehension [7,8]. However, manual simplification is labor-intensive and not scalable in routine practice. The innovative aspect here is using AI (LLMs) to do this at scale and on-demand. Generative AI has only recently become capable enough to handle such tasks with reasonable accuracy. Zaretsky et al [8] provided evidence that an LLM (GPT-4 via Azure) can reliably simplify discharge summaries while maintaining content integrity. They did highlight safety concerns—in 18 of 100 reviews, physicians noted some missing or inaccurate information in AI outputs. This underscores the importance of having a human in the loop, as we have in our protocol. Our results will contribute real-world data on whether an AI-assisted workflow can be integrated feasibly without error-induced AEs.

Another related area is the use of patient question prompt lists or decision aids to improve communication. Those interventions provide patients with structured information and questions to consider, often leading to improved question-asking and involvement. Our AI summary could function similarly to a tailored information sheet; it might even prompt patients to ask about things they read. We will observe qualitatively if patients in the intervention ask more questions. If so, that could be an added benefit—engaged patients often lead to more accurate diagnoses and more concordant treatment plans [2].

In terms of health outcomes, our trials are not measuring long-term outcomes like adherence or health status. But literature ties improved communication to those outcomes. For example, a meta-analysis by Jahan and Siddiqui [14] found that good physician communication is associated with higher adherence to treatment (odds of adherence were 2.16 times higher when patients rated their physician’s communication as excellent). While beyond our scope, it is conceivable that if patients understand their condition and instructions better (through the summary and ensuing discussion), they will be more likely to follow medication and follow-up plans. We plan future research to track such outcomes.

### Public Health and System Implications

Health literacy has been called “the currency of health” in modern health care. Germany, like many countries, has recognized the need to improve health literacy at a population level [1]. Our intervention is one piece of that puzzle—a tool that health care providers can use to ensure each patient, regardless of background, receives information in an understandable form. If our trials show positive results, it would support wider implementation of AI-generated patient-friendly documents across hospitals and clinics. This could be particularly impactful in systems with high patient throughput and limited time, such as busy outpatient practices. By making written communications clearer, the onus on the doctor to cover everything orally in limited time might lessen, as patients come in with some pre-understanding.

From a system perspective, one might worry that providing these summaries is extra work or cost. However, thanks to AI automation, once set up, generating a summary takes only seconds and could be triggered as part of the electronic health record workflow. The physician’s time to review the summary for accuracy is a few minutes—likely offset by time saved in repetitive explanations. And the cost of using the AI (computing cost) is minor per document—perhaps a few cents to a couple of euros depending on length and model pricing. There is also no external funding for this study, meaning this concept is being developed without pharmaceutical or large grant backing—a testament that it is a practical solution emerging from clinical need and tech opportunity, rather than a commercial product push. If effective, we imagine no difficulty in convincing hospital administrations to adopt it, given the relatively low cost and alignment with quality improvement goals (some countries might even incorporate it into guidelines for discharge processes to improve patient comprehension).

Another important aspect is generalizability. While this study is in a neurosurgery context with German-language documents, the principle is applicable to any specialty and any language where a robust translation model exists. Chronic illness management, for example, could benefit—patients with diabetes or cancer often receive complex written instructions, and simplifying those could empower them in self-care. Primary care referrals or interspecialist letters could also be translated so patients fully know what is being communicated about them. On a global level, organizations like the Organisation for Economic Co-operation and Development emphasize patient-centered care and health literacy; our approach directly operationalizes some of the Organisation for Economic Co-operation and Development’s recommendations for using digital tools to improve communication and patient engagement. It exemplifies how digital health innovation can tackle the enduring issue of jargon-filled health care.

### Potential Challenges and Limitations

It is important to consider potential limitations and how they will be addressed.

#### Accuracy of AI Output

While we have a verification step, there is a risk that an AI-generated summary omits a nuance or contains a subtle error. If not caught, this could mislead a patient. For instance, if a summary accidentally downplayed a serious finding, the patient might not realize its importance. We mitigate this with human review and by instructing doctors to double-check understanding. In our future results, we will audit how often corrections were needed. If too many corrections are needed, that could limit scalability. However, given the continuous improvement of LLMs, we expect accuracy to only improve over time. Our current safety plan appears robust for trial purposes.

#### Effects on Consultation Dynamics

We assume the effect is positive, but it is possible some doctors or patients might react unexpectedly. A doctor might feel that the patient’s preknowledge encroaches on their explanatory routine, or a patient might feel overloaded if they read a lot before the talk. It is a delicate balance—one could liken it to giving patients laboratory results directly before talking to the doctor; some studies show patients prefer knowing results beforehand, while others caution that it can raise anxiety. Our trials will provide insight on this. Through the FAPI and qualitative feedback, we will see if any negative sentiments arise, for example, a patient could say “reading it alone made me worried.” We believe the net effect is beneficial as long as the subsequent conversation addresses any anxiety the information caused. Indeed, knowing what to be worried about can lead to addressing it head-on with the physician, which is ultimately good.

#### Generalizability to Lower Literacy Populations

This study requires German proficiency. Those with very low literacy might still struggle, even with a simplified summary, although our summaries aim for fairly low reading level. If someone cannot read at all, our intervention does not help, and they would be excluded. In practice, family members could read to them, but we did not formalize that. Thus, the intervention mostly aids those who can read basic German but not medical German, which is a large group. Future solutions could include audio or video explanations, with AI generating spoken or visual content. This is beyond our current scope but is worth exploring.

#### Two Trials Versus One

We chose to run two separate trials for two scenarios. This is both a strength, covering more ground, and a complexity. It is possible the effect size differs between them. For instance, outpatients might benefit more because they have time to process information before making a decision, whereas inpatients at discharge may be still recovering and less able to absorb written information. Alternatively, inpatients might have a more immediate need to understand postoperative care. If one trial shows significant improvement and the other does not, interpretation will need to consider contextual differences such as pain, stress, and urgency. However, each trial on its own is powered and important. We will report them separately, as well as discuss combined lessons. We consider them as complementary pieces of evidence. Running two complementary RCTs allows us to capture distinct communication inflection points: preparing for treatment decisions in outpatients (AI-INFOCARE) and understanding postsurgical instructions at discharge (AI-MEDTALK). These contexts pose different informational and emotional demands. Analyzing both separately and in pooled form strengthens external validity and clarifies whether effects generalize across settings or are context-dependent.

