### Sample Size and Power Calculation

We determined the target sample size of 300 patients per trial (150 per arm) through power analysis based on the primary outcome (FAPI score). From previous studies using the FAPI/QQPPI in similar settings, we estimate the mean (SD) FAPI score in usual care to be approximately 3.5 (SD 1.0) on the 5-point scale. We consider an increase of 0.3-0.5 in the mean score (with 0.5 being a medium effect, roughly half an SD) to be a clinically important improvement in communication quality. To detect a difference of 0.5 with 80% power at a 2-sided α of 0.05 using a 2-sample *t* test (2-tailed), approximately 63 patients per group are required. To be conservative and account for potential dropout or non-evaluable responses (eg, incomplete questionnaires), we inflated the sample. Our goal of 300 participants per trial (150 per arm) provides >90% power to detect an effect size of *d*=0.5 and approximately 80% power to detect a smaller effect of *d*≈0.4. This sample also provides ample power (>80%) for detecting differences in secondary outcomes, such as a 10-point difference in the 0-100 scaled DDPRQ-10 or approximately a 1-point difference in the understanding rating. We do not plan an interim efficacy analysis, but an internal check of assumptions, such as variance, will be conducted after approximately 50% enrollment to ensure the sample size remains adequate. Given the consecutive recruitment strategy, we anticipate reaching 300 patients in each trial within the planned 6-month recruitment window, as the neurosurgery service sees dozens of new patients weekly and discharges dozens monthly, with a good proportion expected to consent.

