### Statistical Analysis Plan

We will first describe the sample using summary statistics (means or medians for continuous variables, frequencies for categorical variables). The two trial populations (outpatient vs inpatient) will be described separately. Baseline characteristics will be compared between arms to ensure that randomization achieved balance; any significant differences will be noted and adjusted for in secondary analyses if needed.

For the primary outcome (FAPI score), we will compare the intervention and control group means using an independent-samples *t* test (or nonparametric Wilcoxon rank-sum test if the distribution is highly skewed, although previous studies suggest near-normal distribution). We will report the mean difference with 95% CI. The primary analysis will be carried out separately for each trial. However, since the interventions and outcomes are identical, we may also perform a pooled analysis across both trials to increase power, including an indicator for trial to account for any systematic differences in context. Our hypothesis test is 2-sided with α=0.05. We anticipate a positive difference (intervention > control).

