### Subgroup and Exploratory Analyses

We plan to explore whether the effect of the intervention differs by subgroups such as age, with older patients potentially benefitting more or less, education level, with those having lower education or health literacy possibly gaining more, and by doctor. To do this, we may run an ANOVA or regression with interaction terms. For example, we will use a linear regression with FAPI score as the outcome, the intervention as predictor, and an interaction term between intervention and health literacy level, if available from a brief screening question, to examine whether the effect varies. These analyses are exploratory and hypothesis-generating.

We will also analyze the results of the two trials side by side to see whether context, specifically outpatient versus inpatient, influences outcomes. If the direction and magnitude of effect are similar across trials, this strengthens generalizability. If one trial shows a different outcome, for instance if in one context the summary is more beneficial, that will be an interesting finding to explore qualitatively.

All analyses will be performed using SPSS (version 28; IBM Corp) and R software (R Foundation for Statistical Computing). Data analysis will commence after all follow-up is complete. No interim analysis for early stopping is planned, as the intervention is low-risk.

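### Nothing in the plan estimates whether the effect differs between the two settings, so a split in significance may be read as a context difference

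*Protocol article*

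**What the plan says.** All references are to the protocol article.

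- **Statistical Analysis Plan.** The primary comparison of FAPI means is an independent-samples t test, run separately in each trial and reported as a mean difference with 95% CI. "Our hypothesis test is 2-sided with α=0.05". A pooled analysis may be added to gain power, "including an indicator for trial to account for any systematic differences in context". No arm-by-trial term is named.
- **Subgroup and Exploratory Analyses.** Optional interaction terms are listed for age, education or health literacy, and doctor. Trial is not among them. The two trials are to be viewed side by side: "If the direction and magnitude of effect are similar across trials, this strengthens generalizability".
- **Two Trials Versus One.** "If one trial shows significant improvement and the other does not, interpretation will need to consider contextual differences such as pain, stress, and urgency". The same paragraph says that separate plus pooled analysis "clarifies whether effects generalize across settings or are context-dependent".

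**The concern.** One significant and one non-significant result is not evidence that two effects differ. The relevant quantity is the difference between the effects, with its own standard error. The article names a split in significance as the event to be explained and offers only contextual explanations. It does not mention chance or an interval for the difference.

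The pooled model does not fill the gap. With a trial main effect alone, the model assumes one common treatment effect. It can sharpen the estimate of that effect, but it cannot show whether the effect depends on setting, which is what the article claims for the analysis.

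Whether findings carry over between pretreatment outpatients and discharged inpatients is one of the stated purposes of running two trials. That conclusion is the one left unprotected.

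**Working it through.** **Inputs**

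- Sample Size and Power Calculation: 150 per arm in each trial, two-sided α of 0.05. For the FAPI, "we estimate the mean (SD) FAPI score in usual care to be approximately 3.5 (SD 1.0) on the 5-point scale", so a difference in points equals d. "We consider an increase of 0.3-0.5 in the mean score" sets the range d=0.3 to 0.5.
- Results: 25 to 30 inpatients per month. Six months gives 150 to 180 patients, or 75 to 90 per arm in AI-MEDTALK.
- Assumptions: SD equal in both trials, no clustering by physician, all patients evaluable.

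**Step 1: the plan's own figures.** About 63 per group for d=0.5 at 80% power reproduces (63 by the normal approximation, 64 by the t test). Power above 90% at d=0.5 with 150 per arm also holds (99.1%). The stated power of roughly 80% at d≈0.4 does not reproduce: 150 per arm gives about 93%. The calculations below use the recomputed power.

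**Step 2: chance that exactly one trial is significant when the true effects are identical.** With p1 and p2 the power of each trial (noncentral t):

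P(discordant) = p1(1 − p2) + p2(1 − p1)

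At d=0.4 with 150 per arm in both: 2 × 0.932 × 0.068 ≈ 0.126.

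| True d in both trials | Power at 150 per arm | Discordant, 150 per arm in both | Discordant, AI-MEDTALK 90 per arm | Discordant, AI-MEDTALK 75 per arm |
|---|---|---|---|---|
| 0.3 | 73.6% | 38.9% | 49.2% | 52.5% |
| 0.4 | 93.2% | 12.6% | 27.5% | 34.3% |
| 0.5 | 99.1% | 1.8% | 9.2% | 14.6% |

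Taking the article's stated 80% power at d≈0.4 at face value would give 2 × 0.8 × 0.2 = 32%.

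The last two columns depend on a six-month window. The Results section also expects recruitment to run to February 2026 or until targets are met, and allows extension. At 25 to 30 inpatients per month, 8 to 9 months gives 200 to 270 patients, or 100 to 135 per arm, and discordance at d=0.4 is then about 15 to 24%.

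**Step 3: what an interaction estimate would give.** With SD 1.0 and 150 per arm in both trials:

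- SE of the difference between trial effects = √(2/150 + 2/150) = √(4/150) = 0.163.
- 95% CI half-width = 1.96 × 0.163 = 0.32 points.
- Difference detectable with 80% power = 2.80 × 0.163 = 0.46 SD.
- Power for a between-trial difference of 0.2 is about 23%.

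With 90 or 75 inpatients per arm, SE = √(2/150 + 2/90) = 0.189 or √(2/150 + 2/75) = 0.200, and the detectable difference is 0.53 or 0.56 SD.

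**Step 4: how often the two readings agree.** In 200,000 simulated pairs with identical effects and 150 per arm, the interaction test rejected in 5% of pairs at every d. Among pairs with discordant significance it rejected in about 12% at d=0.3 and 23% at d=0.4. At those effect sizes, most splits would be recognised as compatible with equal effects.

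**The case against.** The strongest case on the other side has four parts.

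1. A reader might infer that the authors will conclude context-dependence from significance alone. The text does not say so. The sentence stands in the limitations part of the Discussion and says that contextual differences must be considered. Significance is not the only stated basis either: direction and magnitude are to be compared, and each trial reports a mean difference with 95% CI. This stands, and it limits the point to what may be inferred. It does not remove the point, because two separate intervals are not an interval for the difference and no criterion for similarity is given.

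2. A reader might infer that identical effects will often be reported as different. Across the article's own effect range the discordance rate falls from 39% to 2% at full numbers, so that wording fits only the low end or a smaller AI-MEDTALK. The rates also count discordant significance, not reported setting differences. This stands.

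3. The low inpatient numbers are a projection that the article itself allows to be overcome by longer recruitment. This stands; the 75 to 90 per arm figures are a scenario.

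4. The form of an optional pooled model is commonly left to the SAP, which the article says is final and which is not shown. This would answer a mere omission. Here, however, the article describes the model, names interactions for other factors but not for trial, and claims for the analysis something that the described model cannot deliver.

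**Conclusion.** The concern holds in a limited form. The article promises to clarify context-dependence, but no analysis it describes estimates the difference between the two treatment effects, and its guidance for a split in significance mentions only context. A setting difference may therefore be read into chance.

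With equal true effects and 150 per arm, a split arises in about 39%, 13% and 2% of cases at d=0.3, 0.4 and 0.5. If AI-MEDTALK reaches only 75 to 90 per arm, the rates are about 49–53%, 27–34% and 9–15%, and lower than that if recruitment is extended. All are upper bounds on wrongly reported setting differences under this reading. They rest on a common SD of 1.0, complete data and no clustering by physician.

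The per-trial primary tests are unaffected. The change should be made, but it concerns the cross-setting conclusion only.

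**What to change.** 1. Make the pooled model a planned secondary analysis with arm, trial and arm-by-trial interaction. Leave it unadjusted, to match the primary t test. Adjustment for age, education and clinician belongs with the sensitivity analyses already listed under Randomization and Blinding.
2. Report the difference between the two trial effects with its 95% CI, and base any statement on context-dependence or generalizability on that interval.
3. Reword Two Trials Versus One so that a split in significance is not itself read as a context difference.
4. State the precision: 80% power only for a between-trial difference of about 0.46 SD with 150 per arm in both trials, or about 0.53–0.56 SD with 75 to 90 inpatients per arm. A wide interval is then inconclusive, not evidence of similarity.

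The cost is one model term and a few sentences. No new data are needed.
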